### 3.8.5 Follow-up 5: Twelve-months from treatment initiation

This follow-up will be done by a RA blinded to treatment allocation. Information will be gathered on participant's smoking outcomes, cravings and withdrawal symptoms, use of the Quitline service and monitor any symptoms of depression. Participants meeting the self-reported abstinence criteria (see 3.9.2) will be asked where they would like to take the CO breath test i.e. in hospital or by having a RA visit them at home. Participants recruited prior to the extension of the trial (i.e. prior to the addition of the 12-month follow-up) will be asked to provide verbal consent for this follow-up during their six-month follow-up call. Only those participants who consent to the 12-month follow-up will receive calls at this timepoint.

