### 3.1 Inclusion Criteria

Adults aged 18 years or over, admitted to participating hospitals with a history of smoking  $\geq$  10 cigarettes per day on average in the four weeks prior to their hospital admission, interested in quitting smoking, willing to use pharmacotherapy and available for a 6 months follow-up post-discharge and willing/capable to provide signed informed consent will be eligible for the study. This study will not recruit any outpatient smokers. Hospitalisation

provides a great opportunity for initiating smoking cessation interventions, firstly because of the 'smoke free' policies in all study sites facilitating quitting, and secondly due to greater patient receptiveness to smoking cessation messages and interventions at a time of perceived vulnerability to negative health outcomes. Moreover, initiation of smoking cessation medications such as varenicline during hospital stay allows close monitoring of patients for any adverse events.

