### 3.8 Follow-up Interviews

Five follow-up interviews will be conducted over the entire course of the study: at weeks one and three of treatment initiation and at three-, six- and twelve- months from treatment initiation. The one- and three- week follow up interviews will be done by the RA involved in the participant's recruitment. These follow-ups will be conducted face-to-face for participants who are still inpatients or via telephone for participants who have been discharged. Participants who are uncontactable via telephone will be sent text messages and emails for their follow-ups. Three-, six- and twelve-month follow-up interviews will be conducted via telephone by an independent RA who is blinded to treatment allocation and who was not involved in the participant's recruitment.. A total of ten attempts will be made to contact the participant for follow-up interviews. Participants' next of kin will also be contacted if the RAs are unable to reach the participants directly. If a participant is unable to be contacted beyond this point they will be noted as 'lost to follow-up' and they will be considered as "smokers" according to the Russell Standard. Participants who successfully complete follow-ups at 3, 6 and 12 months will be reimbursed for their time via a gift voucher that will be provided at the 12-month follow-up.

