### 4.2 Data Analysis

Data will be stored in a suitable database (e.g. REDCap™, ACCESS™) and exported for analysis in Statistical Package for Social Sciences (SPSS) (version 23.0; IBM, Armonk, NY) and Stata (ver 15, StataCorp, College Station, TX). As recommended by the Russell Standard, all randomised patients will be accounted for in the intention to treat (ITT) analysis. Participants with missing outcomes at follow-up or whose self-reported abstinence was not biochemically validated will be considered as smokers. Sensitivity analyses using multiple imputation methods will also be carried out. Deceased participants will be excluded from

analyses. In a supportive analysis of the primary efficacy endpoint, an analysis will also be conducted on the per protocol set, which excludes patients with any major protocol deviations.

Logistic regression analyses will be used to examine the efficacy of intervention on the primary outcome, after testing homogeneity between hospitals using a random effects meta-analysis. In the event of heterogeneity, a more robust model incorporating clustering by hospital will be fitted. The effect of intervention on continuous abstinence at 6 months will be tested in pre-specified subgroups (per hospital, nicotine dependence, highly motivated versus moderately motivated smokers and men versus women) using models fitted for each subgroup containing main effects for intervention and subgroup and an interaction between them. Statistical significance will be considered at a two-sided p value of 0.05.

All randomised participants who take at least one dose of the treatment medications will be included in the safety analysis. A chi-squared test will be done to compare the frequency of treatment withdrawal between the treatment and comparator arms. The number of participants discontinuing treatment prematurely for any reason will be summarised by treatment group and by reasons for discontinuation.

The incidence of all suspected adverse events will be summarised by treatment group under the following categories: type, severity, action taken and outcome. Severity of adverse events will be reported using the CTEAE grading scale (v5.0). The causality of the adverse events will be determined using the Noranjo algorithm.

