| 
*Employed: full-time, part-time or casual; Unemployed: student, unemployed, home-duties, disabled, unable to work, retired/pensioner
 
†Other reasons for hospital admission include: conditions of the skin and soft tissues, reproductive, lymphatic, endocrine, urinary or nervous systems
 
PHQ-9: Patient Health Questionnaire-9
 |  |  |  |

819

820 The effectiveness analyses will be by intention to treat (ITT) and participants lost to follow-  
821 up will be regarded as smokers. Deceased participants will be excluded from analyses.

822 Abstinence outcomes (primary and secondary) at 3, 6 and 12 months will be estimated in  
823 each treatment arm. Logistic regression models (unadjusted) will be used to examine the  
824 efficacy of intervention on the primary and secondary abstinence outcomes at each follow-  
825 up visit, after testing homogeneity between hospitals using a random effects meta-analysis.  
826 In the event of heterogeneity, generalised estimating equation models incorporating  
827 clustering by hospital will be fitted.

828

829

830  
831  
832  
833  
834  
835  
836  
837  
838  
839  
840  
841  
842  
843  
844

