Deceased participants at each time-point will be excluded from those specific analyses. All analyses will be adjusted for baseline HSI score.

HSI and PHQ-9 score differences from baseline to 3, 6 and 12 months will be compared between the treatment groups using Mann-Whitney U tests.

**Table 3: Heaviness of Smoking Index and Patient Health Questionnaire-9 score differences from baseline to 3, 6 and 12 months**

| Outcome          | Baseline     |         | 3-months     |         | 6-months     |         | 12-months    |         |
|------------------|--------------|---------|--------------|---------|--------------|---------|--------------|---------|
|                  | Intervention | Control | Intervention | Control | Intervention | Control | Intervention | Control |
| HSI score |              |         |              |         |              |         |              |         |
| HSI score | ----         | ----    |              |         |              |         |              |         |

|                                                   |      |      |  |  |  |  |  |  |
|---------------------------------------------------|------|------|--|--|--|--|--|--|
| (% participants showing improvement) † |      |      |  |  |  |  |  |  |
| PHQ-9 score                                       |      |      |  |  |  |  |  |  |
| PHQ-9 score (% participants showing improvement)  | ---- | ---- |  |  |  |  |  |  |

860 \*Indicates significant differences ( $p < 0.05$ ) between the intervention and control groups. †Follow-up score  
861 lower than baseline score indicates improvement

862  
863  
864  
865  
866  
867

868 A data safety and monitoring board (DSMB) provided oversight of adverse event data on a  
869 periodic basis. For the primary safety outcome, the proportion of reported adverse events  
870 occurring between treatment initiation and over 12-month follow-up will be compared  
871 between the treatment groups using a  $\chi^2$  test or Mann-Whitney U tests, as appropriate.

872 **Table 4: Adverse events experienced by treatment group**

| Outcome                                                              | Intervention | Control | P-value |
|----------------------------------------------------------------------|--------------|---------|----------------|
| Adverse events experienced at week 1 * , n (%)            |              |         |                |

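### Pre-extension participants who do not consent at the six-month call are not called at 12 months, but the protocol counts their missing outcomes as smoking and the SAP leaves their coding unclear, so 12-month abstinence can be understated

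*Combined protocol and SAP*

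**What the plan says.** **Commitment at entry.** Protocol section 3.1 requires participants to be "available for a 6 months follow-up post-discharge".

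**The added visit.** Under protocol section 3.8.5, participants recruited before the extension "will be asked to provide verbal consent for this follow-up during their six-month follow-up call", and "Only those participants who consent to the 12-month follow-up will receive calls at this timepoint".

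**Missing outcomes, protocol.** Section 4.2 states that "all randomised patients will be accounted for in the intention to treat (ITT) analysis" and that "Participants with missing outcomes at follow-up or whose self-reported abstinence was not biochemically validated will be considered as smokers". Deaths are the only exclusion. The section also promises sensitivity analyses by multiple imputation, without naming a model, a time point or this group.

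**Missing outcomes, SAP.** The Statistical Analyses section applies intention to treat to abstinence at 3, 6 and 12 months and counts participants lost to follow-up as smokers. The note under Table 2 adds: "Deceased participants at each time-point will be excluded from those specific analyses". Multiple imputation is not mentioned.

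**What counts as lost.** Protocol section 3.8 allows ten contact attempts and an approach to next of kin. It then says: "If a participant is unable to be contacted beyond this point they will be noted as" lost to follow-up, and hence a smoker.

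**The concern.** Counting missing participants as smokers is a convention for people who were sought and could not be reached. The extension creates a different group: people who met their original six-month commitment and were then not followed, either because they declined more calls or because they were not reached at the call where consent was sought. Their missing 12-month outcome depends partly on when they were recruited.

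Followed literally, the protocol records a CO-verified six-month abstainer in this group as a 12-month smoker. The SAP could be read differently, because someone who was never called does not fit the section 3.8 definition of lost to follow-up. Two analysts could therefore produce different 12-month counts from the same data. At stake are the 12-month abstinence rates, the difference between arms, and any reader's impression of how much abstinence is lost between 6 and 12 months.

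**Working it through.** **1. Who can be misclassified**

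| Pre-extension participant | Protocol 4.2 | SAP with protocol 3.8 | Correct for continuous abstinence to 12 months? |
|---|---|---|---|
| Smoking at 6 months, not called at 12 | Smoker | Not stated | Yes, already a failure |
| Not reached at 6 months, so no stated route to consent | Smoker | Smoker at 6 months; 12 months not stated | Consistent with the 6-month coding |
| Abstinent at 6 months, declined, later relapsed | Smoker | Not stated | Yes |
| Abstinent at 6 months, declined, stayed abstinent | Smoker | Not stated | **No** |
| Consented, not reached after ten attempts | Smoker | Smoker | By convention |

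For continuous abstinence only the fourth row is misclassified. For 7-day point prevalence the group is somewhat wider, because a smoker at 6 months may be abstinent at 12.

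**2. The plan's own figure**

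Inputs from protocol sections 4.1 and 4.2: control rate 23%, difference 15 points (so 38%), two-sided 5%, power 80%. The pooled-variance formula, with mean rate 0.305, gives

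n = [1.960·√(2·0.305·0.695) + 0.842·√(0.23·0.77 + 0.38·0.62)]² / 0.15² = (1.276 + 0.541)² / 0.0225 ≈ 147 per arm.

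With the continuity correction: (147/4)·[1 + √(1 + 4/(147·0.15))]² = 160 per arm. This reproduces the stated figure. It contains no allowance for dropout. Without the continuity correction, 160 per arm gives 83.3% power.

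**3. Effect of the rule, equal non-consent**

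The documents give neither the number recruited before the extension nor the number who declined. Let q be the share of true 12-month abstainers in an arm who are not called (an assumption). The recorded rate is p·(1 − q). The planning rates serve only as a scale for true 12-month abstinence.

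| q, both arms | Control | Intervention | Difference (points) | Risk ratio | Odds ratio | Power, 160 per arm |
|---|---|---|---|---|---|---|
| 0 | 23.0% | 38.0% | 15.0 | 1.65 | 2.05 | 83.3% |
| 10% | 20.7% | 34.2% | 13.5 | 1.65 | 1.99 | 77.5% |
| 20% | 18.4% | 30.4% | 12.0 | 1.65 | 1.94 | 70.7% |

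Example at q = 20%: odds ratio = (0.304/0.696) / (0.184/0.816) = 0.437/0.225 = 1.94. The factor (1 − q) cancels in the risk ratio.

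**4. Unequal non-consent (assumed)**

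- 20% intervention, 10% control: 30.4% vs 20.7%, difference 9.7 points, odds ratio (0.304/0.696)/(0.207/0.793) = 1.67.
- 10% intervention, 20% control: 34.2% vs 18.4%, difference 15.8 points, odds ratio (0.342/0.658)/(0.184/0.816) = 2.31.

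The true odds ratio is 2.05 in both cases, so the bias can run in either direction.

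**5. How large q might be**

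Roughly, q is the share of abstainers recruited before the extension times their refusal rate. If half were recruited early and 10% refused (both assumed), q = 0.5·0.10 = 5% and the difference is 15·0.95 = 14.25 points. Reaching q = 20% with half recruited early would need 40% refusal.

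**The case against.** The strongest defence has four parts.

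- **The participants were asked.** Consent is sought at the six-month call, so decliners were reached and said no, and those not reached had been sought. It would be tempting to say that nobody looked for these people. The documents do not support that; what is true is that decliners are not called at 12 months.
- **The misclassified group is narrow.** For continuous abstinence it is limited to six-month abstainers who declined and stayed abstinent. If every decliner relapsed, the rule causes no bias. This stands, and it limits the size of the problem.
- **The planned effect measure moves little.** SAP Table 2 reports odds ratios, and under equal non-consent the attenuation is modest even at q = 20%. This also stands. It does not cover the absolute rates, or unequal non-consent.
- **Multiple imputation is already planned.** It is only a sensitivity analysis, has no rule for this group, and is absent from the SAP. The main 12-month abstinence result would still carry the misclassification.

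A reader might also infer that every 12-month result is biased, or that the trial's conclusion about durability must be wrong. Neither follows. The smoker rule applies to abstinence only. HSI and PHQ-9 change, Quitline use and use of other therapies lose data from non-consent but are not recoded. No formal comparison of relapse between 6 and 12 months is planned, and bias is possible rather than certain.

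**Conclusion.** The point holds for the 12-month abstinence rows of SAP Tables 2 and 6. The protocol's rule, applied as written, can record unfollowed six-month abstainers as smokers, and the SAP does not settle whether it applies to them. Whenever any uncalled participant is in truth abstinent, the recorded 12-month rate is too low. With equal non-consent the risk difference shrinks in proportion, the odds ratio is modestly attenuated and the risk ratio does not change. With unequal non-consent the comparison can be biased either way.

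The figures rest on assumed values of q and on planning rates used as a scale; the documents do not allow a single estimate. The documents give no separate 12-month power target, so the power values illustrate the loss and do not show that a stated target is missed. The 6-month primary outcome is unaffected. The matter deserves correction because the rule as stated gives a wrong record for identifiable people and the remedy needs no new data.

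**What to change.** In the SAP, for the 12-month abstinence outcomes:

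1. Define two separate categories: not consented under the extension, and lost after contact attempts. State the 12-month denominator.
2. Keep missing-as-smoker for the second category and, for continuous abstinence, for anyone already non-abstinent or unreached at 6 months.
3. For six-month abstainers not followed under the extension, and for non-consenters in the point-prevalence outcome, apply the multiple imputation already planned in protocol section 4.2, using arm, six-month status, HSI and hospital.
4. Show the result with all missing outcomes counted as smoking beside the imputed result.
5. Report the number of non-consenters by arm with their six-month status, so that readers can see whether non-consent was balanced.

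The cost is SAP wording and one imputation model on data already collected. The downside is that the imputed result assumes missingness at random given those variables. It would overstate abstinence if decliners relapse more often than comparable participants who were followed, which is why both results should be shown.

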## 3.9 Assessments and Main Outcome Measures

Data will be collected upon consent and at each of the five follow-ups.

### 3.9.1 Baseline Data

Information collected at the time of the baseline interview after obtaining written informed consent will include the following:

- Demographic information: contact details, country of birth, age, gender, education, employment status, living arrangement and possession of concession cards
- Smoking habit: age when they started, average number of cigarettes smoked per day, previous quitting experiences and methods used, perceptions about smoking cessation and willingness/confidence to quit

- Nicotine dependence: nicotine dependence will be assessed using the 2-item Heaviness of Smoking Index (HSI)
- Psychological distress: presence and extent of psychological distress will be assessed using the Patient Health Questionnaire (PHQ-9)
- Participant's motivation to quit smoking and confidence to quit smoking will be assessed using a 10 point scale with one being 'very low' and 10 being 'very high'
- Medical history: including a list of all current medications and medical conditions

### 3.9.2 Primary Outcome Measure

The primary outcome will be biochemically verified continuous abstinence from 2 weeks to 6 months from treatment initiation. A 2-week period will be allowed on treatment commencement to match the recommendation in the varenicline product information sheet. Participants who self-report abstinence (i.e. self-report smoking no more than five cigarettes, including the use of non-combustible tobacco products and electronic cigarettes) over this period (i.e. weeks 2-26) will be asked to perform a carbon monoxide (CO) breath test. CO levels will be measured by trained RAs blinded to treatment allocation, using using a hand held piCO+ Smokerlyzer (Bedfont Scientific, Maidstone, Kent, UK) during a hospital or home visit. Participants with a CO level <10ppm will be considered abstinent. Sensitivity analysis will be performed using a lower CO cut-off of <5ppm.

### 3.9.3 Secondary Outcome Measures

The secondary outcome measures are:

- Self-reported continuous abstinence from 2 weeks to three-, six- and twelve- months from treatment initiation
- CO verified continuous abstinence from 2 weeks to 12 months from treatment initiation for participants who self-report abstinence at this follow-up
- Self-reported 7-day point prevalence abstinence (i.e. smoking not even a puff in the past 7 days on the day of follow-up) measured from 2 weeks to 3, 6 and 12 months from treatment initiation
- CO verified 7-day point prevalence abstinence from 2 weeks to 6 and 12 months from treatment initiation for participants who self-report abstinence at these follow-ups
- Participant self-reports of withdrawal symptoms and cravings using the Mood and Physical Symptoms Scale (MPSS)
- Self-report of treatment adherence using the 8-item Tool for Adherence Behaviour Screening (TABS)
- Adverse events experienced from study medications
- Change in psychological distress
- Number of Quitline sessions attended/received
- Other health resources used including emergency department visits, GP visits (for smoking cessation), over-the-counter medicines used as well as the use of other smoking cessation therapies and alternate products

### 3.10 Withdrawal Criteria

All participants are strongly encouraged to complete the study, however there may be certain situations in which withdrawal from the study may be appropriate. Participants may withdraw from the study if one or more of the following occurs:

- The participant experiences any serious adverse event (SAE) or reaction due to the use of varenicline or NRT lozenges. Prior to treatment discontinuation, input from the treating medical team and end point evaluation committee will be sought in establishing the association between treatment exposure and adverse events. The DSMB will review all such cases and make the final judgement on causality.
- If a female participant becomes pregnant during the course of treatment
- If a participant's health status changes significantly and the study medications are no longer in the best interest of the participant
- The lead investigators or health professionals perceive, for any reason, that the study is no longer in the best interest of the participant

A participant wishing to withdraw from the study will be requested to fill a 'withdrawal form' for record purposes. Once withdrawn, the participant will not be contacted for further data collection, however their available data will be included in the Intension-to-treat analysis. If withdrawal is a result of an adverse drug reaction, the participant will be followed until the adverse reaction resolves or there is return to clinically acceptable medical status.

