## 4. Statistical Considerations

### 4.1 Sample Size

To show a difference of 15% in continuous abstinence between study arms (based on continuous abstinence rate of 23% in varenicline trials) at the 5% level of significance with 80% power, we will need 160 subjects per arm. i.e. 320 participants in total from the six hospitals, , 160 in each of the study arms. The primary analysis will be intention to treat (ITT) and lost to follow-up participants will be regarded as smokers.

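### Section 3.10 does not separate stopping study medication from leaving the study, so a withdrawal for a drug-related reason before month 6 counts as smoking whatever the participant's true status

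*Combined protocol and SAP*

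**What the plan says.** Protocol section 3.10 (Withdrawal Criteria) lists four grounds on which a participant may leave the study. Three concern the drug: a serious adverse event or reaction due to varenicline or lozenges, pregnancy during treatment, and a change in health such that "the study medications are no longer in the best interest of the participant". The fourth is a judgement by investigators or health professionals that the study itself no longer suits the participant. The first item also speaks of discontinuing treatment, so the two ideas appear together without being distinguished.

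The section continues: "Once withdrawn, the participant will not be contacted for further data collection". Data already collected stay in the intention-to-treat analysis. If the cause was an adverse drug reaction, the participant is followed until it settles or their condition is clinically acceptable.

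Section 3.9.2 defines the endpoint: "The primary outcome will be biochemically verified continuous abstinence from 2 weeks to 6 months from treatment initiation". Section 4.2 (Data Analysis) then states: "Participants with missing outcomes at follow-up or whose self-reported abstinence was not biochemically validated will be considered as smokers". The SAP (Statistical Analyses) likewise treats participants lost to follow-up as smokers.

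Section 4.2 also promises multiple-imputation sensitivity analyses, a summary of premature treatment discontinuation by arm and reason, and a chi-squared comparison of treatment withdrawal between arms. The SAP does not mention imputation, and none of its eight table shells reports discontinuation or withdrawal.

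**The concern.** An intention-to-treat comparison of abstinence needs smoking status from everyone randomised, whether or not they kept taking the drug. Reactions, pregnancy and unsuitable medication are reasons to stop a drug. They are not in themselves reasons to stop asking about smoking. Section 3.10 makes them grounds for leaving the study and ends outcome collection on leaving. No section says that a participant who stops medication stays in follow-up for smoking status.

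Combined with the missing-as-smoker rule, a person who stops medication because of a reaction, is recorded as withdrawn and stays abstinent becomes a failure on the primary outcome. The missing data are then partly a consequence of treatment. Only the intervention arm receives nicotine lozenges, and Appendix C lists nausea, vomiting, indigestion, constipation, headache and insomnia for both varenicline and the lozenges, so withdrawal could plausibly differ by arm. If it does, the treatment comparison mixes abstinence with tolerability. Even equal withdrawal shrinks the absolute difference, because it removes more successes from the arm with the higher quit rate.

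**Working it through.** **Inputs from the documents.** Control rate and difference, section 4.1: "To show a difference of 15% in continuous abstinence between study arms (based on continuous abstinence rate of 23% in varenicline trials", which implies 38% in the intervention arm. Size, section 4.1: "at the 5% level of significance with 80% power, we will need 160 subjects per arm". Sidedness, section 4.2: "Statistical significance will be considered at a two-sided p value of 0.05".

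**Reproducing the plan's figure.** For two proportions with pooled variance under the null, p̄ = (0.23 + 0.38)/2 = 0.305:

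n = [1.960·√(2·0.305·0.695) + 0.842·√(0.23·0.77 + 0.38·0.62)]² / 0.15² = 146.7, so 147 per arm.

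With the continuity correction, (n/4)·[1 + √(1 + 4/(n·0.15))]² = 159.8, so 160 per arm. This matches the protocol exactly. The SAP's 22.5% control rate with the same difference gives 159. The 160 therefore contains no allowance for withdrawal. Without the continuity correction, as in all power figures below, power at 160 per arm is 83.3%.

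**Bias formula.** Let w be the share withdrawn before month 6 without outcome follow-up, and a the true abstinence among them, by arm (I, C). Each withdrawn abstainer is recoded as a smoker, so

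bias in the risk difference = −(wI·aI − wC·aC).

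This is zero under equal withdrawal only if the withdrawn quit at the same rate in both arms.

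**Assumed rates.** The documents give no withdrawal rate, so every w and a below is an assumption. In the first set the withdrawn quit at their arm's planned rate (aC = 0.23, aI = 0.38). Example for 5% control and 10% intervention: 0.10·0.38 − 0.05·0.23 = 0.038 − 0.0115 = 0.0265, so the expected difference is 15.00 − 2.65 = 12.35 points.

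| Withdrawn, control / intervention | Observed rates | Difference (points) | Odds ratio | Power, 160 per arm |
|---|---|---|---|---|
| 0% / 0% | 23.00% / 38.00% | 15.00 | 2.05 | 83.3% |
| 5% / 5% | 21.85% / 36.10% | 14.25 | 2.02 | 80.5% |
| 10% / 10% | 20.70% / 34.20% | 13.50 | 1.99 | 77.5% |
| 5% / 10% | 21.85% / 34.20% | 12.35 | 1.86 | 69.3% |
| 5% / 15% | 21.85% / 32.30% | 10.45 | 1.71 | 55.7% |
| 10% / 5% | 20.70% / 36.10% | 15.40 | 2.16 | 86.7% |

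**If the withdrawn quit at half their arm's rate** (aC = 0.115, aI = 0.19), 5%/10% gives 15 − 1.325 = 13.7 points and 76.9% power; 5%/15% gives 15 − 2.275 = 12.7 points and 71.2% power.

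**If there is no true effect** (23% in both arms, withdrawn at the same rate), 5%/15% gives observed rates of 21.85% and 19.55%. That is a spurious −2.3 points, with a two-sided rejection rate of about 8%.

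In head counts, 5%, 10% and 15% of 160 are 8, 16 and 24 participants.

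**The case against.** The strongest reply is that section 3.10 is permissive. Participants may withdraw and are encouraged to complete the study, and the no-contact sentence follows the one about a participant who wishes to leave. On that reading it simply respects a wish to end participation. The follow-up sections do not make calls conditional on still taking the drug, section 6 speaks of discontinuing treatment after safety concerns and not of leaving the study, and section 4.2 tabulates discontinuation separately. The fourth ground is a study-level reason. Missing-as-smoker is the declared Russell Standard convention, and imputation is planned.

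Much of this stands, and it rules out three stronger readings that a reader might infer.

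- That stopping the drug automatically means withdrawal: the text does not say so. The fault is that it does not separate the two.
- That withdrawn participants are never contacted again: adverse-reaction withdrawals are followed until the reaction settles. What ends is outcome collection.
- That the rule necessarily biases against the combination: that needs more abstainers to be lost from the intervention arm, and no figure in the documents shows this. At 10% control against 5% intervention the difference is inflated.

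What the reply does not supply is a sentence that keeps people who stop medication in outcome follow-up. Nor does imputation close the gap. No method or assumption is given, the SAP drops it, and it can only model smoking status that was never collected.

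**Conclusion.** The concern holds in this limited form. As written, the plan allows a drug-related withdrawal before month 6 to become a primary-outcome failure regardless of smoking status, and it does not commit to collecting the data that would prevent this.

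The size cannot be known from the documents. Under the assumed rates, equal withdrawal of 5% to 10% is a modest loss; at 5%, power remains just above the planned 80%. An excess of 5 to 10 points in the intervention arm over 5% in control matters more. It gives 12.4 to 10.5 points and 69% to 56% power if the withdrawn quit at their arm's rate, or 13.7 to 12.7 points and 77% to 71% power if they quit at half that rate. The direction depends on which arm loses more abstainers.

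The point should be fixed but does not invalidate the design: withdrawal is optional, the missing-data rule is declared, and the remedy is small.

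**What to change.** Split section 3.10 into (a) stopping study medication and (b) withdrawing consent to follow-up. State that participants under (a) keep all scheduled calls and the 6- and 12-month CO tests unless they decline, and that only (b) ends data collection. Give the withdrawal form a separate box for each. Leave the clinical reasons for stopping unchanged.

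In the SAP, add a table of medication stops and study withdrawals by arm, reason and timing (before or after month 6). Carry over the multiple imputation from section 4.2 with its model and assumptions stated.

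The SAP's Sample size section describes recruitment in the past tense, so some or all follow-up may be complete. Where it is, report those counts and add a tipping-point analysis to the imputation: vary the assumed abstinence among the withdrawn separately in each arm and show where the conclusion changes.

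The cost is protocol, SAP and form wording, plus a few follow-up contacts of a kind already scheduled for every participant.
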